### Sample size

The sample size for this population-based study is fixed by the available number of eligible childhood cancer survivors. We previously identified 1724 childhood cancer survivors (53% of the POGONIS subset of 3268 childhood cancer survivors at risk for breast cancer, colorectal cancer, and/or cardiomyopathy) who were overdue for one or more of the recommended breast, colon, and/or cardiac tests as of 28 February 2021. Therefore, we anticipate allocating at least 862 individuals to each trial arm (intervention and control). Based on our prior analyses of administrative data [34], we estimate the uptake of recommended tests in a 12-month period will be 15% without any intervention (i.e., control arm proportion). Our anticipated sample size is sufficient to detect an absolute increase in the proportion of childhood cancer survivors with one or more tests completed as small as 6% (or a relative increase of 1.4) with 90% power in our intention-to-treat analyses. While a difference of 6% is considered relevant and important on a population level, it is expected that among those fully exposed to the intervention, the effect could be substantially higher. Loss-to-follow-up is anticipated to be minimal given the use of administrative data for outcomes.

### Ethical considerations

Our approach meets ethical principles [35] as outlined in the Canadian Tri-Council Policy Statement: Ethical Conduct for Research Involving Humans–TCPS 2 (2022) and has been approved by Clinical Trials Ontario [####]. We used a similar approach in our recently published provincial registry-based trial of reminders for heart attack survivors [36].

A delayed intervention for the control group by 1 year will allow us to determine whether the intervention has an effect without putting the control group at undue risk by withholding critical health information (given current equipoise) and without creating substantial selection bias.

Ontario Health’s current approach to identifying and contacting patients for research purposes also involves using administrative datasets. Ontario Health is designated a “prescribed entity” in Sect. 45(1) of the PHIPA, 2004. As a prescribed entity, Ontario Health is authorized to collect personal health information from health information custodians without the consent of the patient, and to use such information for the purpose of analysis or to manage, evaluate, or monitor the allocation of resources. Ontario Health is also authorized to use personal health information for planning purposes for all or part of the health system, including the delivery of services. Participants cannot opt out of the analysis of these de-identified linked datasets.

Randomization and analysis of de-identified administrative data following an intent-to-treat protocol will occur without prior consent, but meets TCPS-2 criteria for this, based on (i) minimal burden or risk of harm from the intervention, (ii) infeasibility of answering the question at hand if prior consent was required, and (iii) provision of a debrief. Specifically, we will send the introductory information to both groups based on their randomized allocation (i.e., immediately or after a delay for the control group). Seeking prior consent from all those eligible for this health system intervention prior to sending them the introductory package would be redundant (because it would explain the reason for contact) and would involve substantial risks for performance bias, threatening the ability to accurately assess the effects of ONLOOP as it would be implemented, without reducing meaningfully any risk to the welfare or autonomy of participants. Upon receipt of the introductory letter, which denotes that ONLOOP is a research study, recipients could then choose to opt-in to receive (or not) the full intervention package and they would choose (or not) to have information sent to their primary care clinician. Finally, in our study invitation letter and on our study website, we offer the option to contact the study team for results as a debrief once the study is complete.

### Process evaluation

Informed by guidance on process evaluations for complex interventions, we will assess intervention implementation fidelity (whether the intervention was delivered as intended), dose (the quantity of intervention implemented), and mechanisms of impact of the intervention [37, 38]. We will seek to understand: (1) how the intervention interacts with its context; (2) the underpinning program theory; (3) how diverse stakeholder perspectives can be included; (4) the key uncertainties; (5) how the intervention can be refined; and (6) whether the effects of the intervention justify its cost.

#### Fidelity and dose

The process evaluation will determine the fidelity of the intervention content (whether the intervention was delivered as intended) and dose (the quantity of intervention implemented). We will identify the proportion of all eligible intervention arm survivors who complete each intervention step: intervention sign-up (i.e., requesting their information toolkit), and whether they completed their surveillance test(s). We will assess factors (e.g., age, sex, location) that may explain their degree of engagement with ONLOOP. In the interviews, fidelity and dose will be further explored to understand the program theory, causal mechanisms, and contextual factors associated with variation of fidelity and dose. For example, we will assess understanding of the information kit, and why survivors may or may not have used their information kit to complete recommended surveillance tests.

### Data collection

At 6 months post-randomization of the study cohort, we will carry out the process evaluation components below with survivors in the intervention arm and with their primary care providers. In the second study invitation reminder letter, we ask survivors who do not consent to the ONLOOP Trial for consent to send them information about the process evaluation interview. They can participate in this interview even if they do not participate in the ONLOOP Trial. We will use Canada Post to mail out process evaluation interview invitations. Survivors and primary care providers will be asked to contact the study team if they are interested in participating. Trained study team members from Women’s College Hospital will obtain informed consent from all individuals interested in participating in an interview.

#### Survivor interviews

We aim to recruit approximately 15 survivors who opted into ONLOOP and 15 who did not opt-in (i.e., non-engagers). All study interviews will last approximately 30–45 min and will be conducted by telephone or Zoom and will be recorded for transcription purposes.

#### Interviews with survivor’s primary care provider

The study team will mail an invitation to approximately 200 primary care providers who received a postal letter or fax regarding their patient’s screening recommendations. We anticipate a sample size of *n* = 15 and will stop recruitment once we reach thematic saturation (no new codes emerge from the analysis). We will purposively recruit physicians whose patients were recommended to receive a mix of cardiac, breast, and colorectal tests. We aim to recruit a diverse group of physicians based on age, location (urban vs rural), and type of practice (Family Health Team vs other).

#### Interviews with aftercare nurses

We will mail an invitation to AfterCare nurses to understand whether survivors were referred to an AfterCare clinic after receiving their ONLOOP Trial invitation. The study team will send an email invitation to each of the lead AfterCare nurses at the 7 sites across Ontario.

#### Physician fidelity check to confirm receipt of information letter by the childhood cancer survivor’s physician

We will assess whether physicians reviewed the physician’s letter. Approximately 6 months after intervention delivery, a research team member at WCH will call a subset of physicians whose patients were randomized to the intervention arm and provide consent to contacting their physicians. Physicians will be sorted by sex and area code, and we will randomly sample from each stratum until 78 physicians have been called. This sample size was calculated based on an anticipated proportion of 30% of physicians remembering receiving the letter, and a margin of error no greater than ± 10%. Each physician selected will be called up to 3 times over the course of one week. Non-respondents to phone calls will be tracked. Physicians who answer the call will be asked whether they received the letter from the study team; those who reviewed the letter will be asked if they can confirm what they thought the main message was, and whether they have any questions for the study team. Our research will not impact the participant’s employment, relationship with provincial organizations, or reputation in any way. It is meant to be informative for the research community and to contribute to the growing and relevant body of research.

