### Analysis

Primary outcome analyses at 12 months will be by intention-to-treat. Descriptive statistics will be used to summarize the baseline and clinical characteristics of participants in each arm. To obtain correct inferences and improve power and efficiency, we will use a logistic regression model to estimate intervention effects, adjusting for sex and number of tests overdue at baseline (the stratification factors) as well as the following pre-specified prognostic factors: rurality, age at diagnosis, and attachment to primary care. The intervention effect will be expressed as an adjusted odds ratio together with a 95% confidence interval. Results will be converted to relative risks and risk differences which will be used to calculate the number needed to treat [33]. The number needed to treat is the inverse of the absolute risk difference.

The primary outcome analysis will be the completion of at least one test, but secondary analyses will explore whether results differ according to the type of test. We will conduct separate analyses for each test among eligible childhood cancer survivors. The secondary outcome of being fully up-to-date according to guidelines at the time of outcome assessment will be analyzed as described for the primary outcome. Health services utilization outcomes (e.g., number of outpatient visits over the prior 12 months or 24 months) will be analyzed using negative binomial regression, adjusting for the stratification factors.

Secondary analyses will consider the subgroup of participants in the intervention arm who are exposed to the full intervention (i.e., those who opt-in to receive their personalized information kit). Subgroup analyses in both the intention-to-treat and per-protocol populations will also be carried out to examine effect modification for the primary outcome by sex, number of tests required (1 vs 1 +), type of test required, rurality, neighborhood-level socioeconomic status, age at diagnosis, current age, and attachment to primary care. Ontario Health will transfer the deidentified study administrative dataset to the Ottawa Hospital Research Institute for analysis.

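### The physician fidelity check stops at 78 physicians called, but 78 matches the number of answers needed for the stated ±10% margin, with nothing allowed for non-response

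*Protocol article*

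**What the plan says.** The Protocol article, under the physician fidelity check in the process evaluation, describes telephoning a subset of physicians of intervention-arm survivors who agreed to physician contact, about six months after delivery. Physicians are sorted by sex and area code, and the stopping rule is: "we will randomly sample from each stratum until 78 physicians have been called". The next sentence presents 78 as a calculated sample size, based on "an anticipated proportion of 30% of physicians remembering receiving the letter" and "a margin of error no greater than ± 10" per cent.

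The section then separates calling from answering. On attempts: "Each physician selected will be called up to 3 times over the course of one week". On those not reached: "Non-respondents to phone calls will be tracked". On who supplies the data: "Physicians who answer the call will be asked whether they received the letter from the study team". It states no replacement of non-respondents and no inflation of the 78 for non-response. It also names no confidence level or interval method.

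**The concern.** The stopping rule and the precision statement count different things. The rule counts physicians called. The margin of error depends on the number who give an answer, because a physician who is never reached says nothing about whether the letter was received. If 78 was calculated as a number of observations, it is being used as a number of attempts, and the stated margin assumes that nearly every call succeeds.

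At stake is the reported precision of one descriptive measure, the proportion of physicians who recall the letter. Fidelity of delivery is a named aim of the process evaluation, and this check is the only process measure for which the article states a precision target. No hypothesis test, threshold or decision is attached to it.

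**Working it through.** **Inputs.** From the physician fidelity check: p = 0.30, margin d = 0.10, 78 physicians called. Assumed: two-sided 95% confidence (z = 1.96). The section gives no level; 95% is the level used for the trial's intervention effect in the Analysis section ("adjusted odds ratio together with a 95% confidence interval"). The response rate is not given, so a range is shown.

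**1. Reproducing 78.**

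Wald: n = z²·p(1−p)/d² = 1.96² × 0.21 / 0.01 = 80.7, so 81. At n = 78 the Wald half-width is 1.96 × √(0.21/78) = 10.17 points.

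Wilson: half-width = z·√[p(1−p)/n + z²/(4n²)] / (1 + z²/n).
- n = 78: 1.96 × √(0.002692 + 0.000158) / 1.0492 = 9.97 points.
- n = 77: 10.03 points.

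So 78 is the smallest number of observations that meets ±10 points by Wilson at 95%. Other choices do not give 78: Agresti–Coull 79, Jeffreys 79, Clopper–Pearson 89, Wald at 90% confidence 57, Wald at 99% confidence 140. The Wilson reading is therefore a good reconstruction, but it remains an inference.

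**2. Margin if 78 are called and only some answer** (p = 0.30, no finite-population correction):

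| Assumed response | Answers | Wilson (± points) | Wald (± points) |
|---|---|---|---|
| 100% | 78 | 9.97 | 10.2 |
| 90% | 70 | 10.5 | 10.7 |
| 80% | 62 | 11.1 | 11.4 |
| 70% | 55 | 11.8 | 12.1 |
| 50% | 39 | 13.8 | 14.4 |
| 30% | 23 | 17.6 | 18.7 |

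**3. Physicians to sample for 78 answers** = 78 / response rate:
- 78/0.70 = 111.4, so 112
- 78/0.50 = 156
- 78/0.30 = 260

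**4. Finite-population correction.** With a frame of N physicians, n = n₀ / [1 + (n₀ − 1)/N], with n₀ = 80.67 (Wald). The article does not give N for this check.
- N = 200: 80.67 / (1 + 79.67/200) = 57.7, so 58 answers, and 58/78 = 74%.
- N = 300: 63.7, so 64 answers (82%).
- N = 400: 67.3, so 68 answers (87%).
- N = 862: 73.8, so 74 answers (95%).

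The 200 is borrowed from the section on interviews with primary care providers, where it is the approximate number of interview invitations and not a stated frame for the calls. The 862 is the anticipated size of the intervention arm; it would apply only if every survivor opted in, agreed to physician contact and had a different physician.

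**The case against.** The strongest objection is that the physicians who were sent a letter form a finite and possibly small group, so a finite-population correction is legitimate. With 200 in the frame, the margin survives a response as low as 74%. This stands as a limit on the claim. A reader might infer that the stated precision holds only if every physician answers, or that it is certain to be missed. The documents support neither, because the response rate and the frame size are both unknown. The correction does not remove the mismatch, however: the article does not invoke one, and a frame of 200 would have led to 58, not 78.

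Second, the basis of 78 is not stated. Level and method are inferred, and the commonest formula gives 81. That is fair, but under Wald the margin is already 10.2 points when all 78 answer, so the alternative does not help the plan.

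Third, the word called might loosely mean reached. The same section uses it for up to three attempts per physician and treats answering separately, so the plain reading is attempts. If reached was meant, the sentence still needs correcting.

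Fourth, the article condenses a fuller protocol, which may hold a replacement rule. That is possible, but the article itself prints a stopping rule and a precision statement that do not agree.

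Finally, a reader might fear that non-answerers will be counted as not recalling the letter, which would bias the proportion downward. Nothing in the article proposes this: only answerers are asked, and non-respondents are tracked. Nor does the check carry the whole explanation of success or failure. Sign-up, test completion and the interviews do most of that work.

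**Conclusion.** The mismatch is real. The rule fixes the number of physicians called, the margin depends on the number who answer, and 78 corresponds to the uninflated number of answers. Without a finite-population correction, any appreciable non-response takes the margin above the stated limit, by roughly 2 points at 70% response, 4 at 50% and 8 at 30% (Wilson, 95%, p = 0.30, response rates assumed). With a correction, the margin may still be met, depending on response and on how many physicians are eligible. The supportable conclusion is that the stated precision has no reserve and may not be met. The consequence is limited to a descriptive process-evaluation estimate; the primary and secondary outcomes and the economic evaluation are unaffected.

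**What to change.** Change one sentence before calling begins, in one of two ways.

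- **Keep 78 calls and restate the margin** for the expected response, for example about ±14 points if half answer. If a finite-population correction is to be used, say so and give the frame size. The only cost is a less favourable stated margin.
- **Count answers instead of calls**: sample until 78 physicians have answered, if the pool of eligible physicians allows. This means sampling about 112 physicians at 70% response and 156 at 50%. The cost is extra short calls. At 30% response it would take 260 physicians, which may exceed the pool, so the eligible number should be checked first.

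Either way, state the confidence level and interval method, and report the response rate beside the recall proportion among those who answered. More calls restore precision but do not remove non-response bias.

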#### Confidentiality

Interviews will be audio-recorded and then transcribed verbatim by an external third party. Any identifiable information (i.e., names of individuals or institutions) will be removed from transcripts to ensure that respondents remain anonymous. Identifiable information will not be used in any study records, except the consent form (which will be stored separately from the other study records). The interview transcripts will be assigned a unique identification code and will be referred to by this code during discussions and in documents. The audio recordings will be stored in a secure location and viewed only by members of the research team. The recordings will be kept until they have been transcribed, and then they will be destroyed. The transcripts will be kept in a secure location for 7 years and then destroyed.

### Analysis of interviews

#### Survivor interviews

We will employ a directed content analysis approach using the domains in the Theoretical Domains Framework (TDF) [16, 39] as deductive codes. The TDF is a comprehensive, theory-informed approach frequently used by implementation scientists to identify the determinants of behaviors in healthcare professionals and patients. Themes will then be developed inductively within and across TDF domains to describe barriers and enablers of key behaviors required as outlined in the program theory. In addition to the TDF, we will use the Social Determinants of Health framework to consider the broader determinants of health in a more comprehensive approach to addressing surveillance adherence [40, 41]. We will use cross-case comparisons, with cases defined at the level of the outcome (i.e., engagement at a given step and completion of surveillance tests) to understand the determinants of impact (or lack thereof). We will also explore how change is being brought about and how this may vary across different contexts and survivors. Analyses will help determine the key components of the intervention that need to be preserved in implementation to maximize the likelihood of achieving the effects found in the evaluation.

#### Physician interviews

We will explore their perceptions of ONLOOP and how they interacted with the intervention. Interviews will be informed by the TDF and will be used to explore barriers and enablers of the key behaviors required as outlined in the program theory [16]. Each behavior related to the desired intervention processes (e.g., reading the recommendation fax, discussing with their patient, ordering tests, setting reminders) will be specified [42] and explored to understand barriers and enablers and to inform intervention refinement [43]. The interview guide will be piloted with two physicians using the “think aloud method” [44] and will be revised as needed.

#### Aftercare nurse interviews

Interviews will explore how the intervention intersected with the survivor aftercare clinics. We will ask nurses about their experiences with survivors who engaged with the aftercare clinics after receiving the intervention materials. The interviews will explore from the aftercare nurses' perspectives how the intervention for survivors complements the aftercare clinics and the ideal way forward for the intervention to exist alongside the aftercare clinics. Transcripts will be analyzed by thematic analysis using inductive coding to describe the manifest and latent content [45]. Inductive coding will be considered on a case-by-case basis. Subsequent levels of coding will involve re-examining the content of the codes and narrowing in on more specific elements discovered in the data during coding. Initial themes will be reviewed and refined to ensure that the themes represent the dataset as a whole and that no themes are missed or over-represented.

### Economic evaluation

We will conduct a cost-effectiveness analysis of ONLOOP compared to the delayed-intervention arm from the perspective of Ontario Health.

We will use a top-down and bottom-up approaches to estimate the costs of developing and delivering the intervention. We will obtain resource use data for developing and implementing the intervention, as well as their unit costs, from program financial records, service level agreements, and the program budget. We will track the time and costs required to deliver the intervention. Costs associated with health care utilization will be derived using cost macros developed at ICES [29]. Consistent with the trial, effectiveness will be measured as the proportion of survivors who complete one or more of the guideline-recommended cardiac, breast, or colon surveillance tests within 12 months after randomization (in accordance with the primary outcome). Analyses will conform to the most recent Canadian guidelines for economic evaluation [46] and current guidelines for such analyses in randomized control trials [47].

The incremental cost and outcome will be estimated using generalized estimating equations, a flexible multivariate regression framework that explicitly allows the modeling of non-normal distributional forms of repeated measures data. We will evaluate the uncertainty of the cost-effectiveness estimates using non-parametric bootstrapping. We will obtain 5000 estimates of costs and outcomes for each option. Results from the bootstrapping exercise will also be used to estimate 95% confidence intervals and depict cost-effectiveness acceptability curves, which show the probability of ONLOOP being cost-effective to a range of potential threshold values that the health system may be willing to pay for an additional unit of effect. We will also perform a budgetary impact analysis [48] to estimate the resources and financial implications of implementing the intervention in Ontario and other Canadian provinces over 5 years. As suggested by our policy stakeholders, we will conduct a scenario analysis by developing a simple simulation model and using data from the trial to project cost and adherence outcomes over a survivor’s lifetime. This scenario analysis could show the potential long-term consequences of the intervention beyond the duration of the trial.

